## Abstract

Facing your fears, or exposure therapy, is an effective psychological intervention for anxiety disorders that is often thought to work through fear extinction learning. Fear extinction learning is a type of associative learning where fear reduces through repeated encounters with a feared situation or stimulus in the absence of aversive outcomes. Laboratory research suggests fear extinction learning is driven by threat prediction errors, defined as when fearful predictions do not eventuate. Threat prediction error and its relationship to exposure therapy outcomes haven’t been studied enough in actual therapy settings. It remains unclear whether prediction error and extinction learning are central mechanisms of exposure therapy. We are conducting a longitudinal and observational study of how threat prediction error during exposure in social anxiety disorder (SAD) treatment relates to session-by-session symptom change and treatment outcome in addition to exposure surprise and learning outcome. We aim to recruit 65 adults with a primary diagnosis of SAD through an outpatient psychology clinic. Participants will receive 12 sessions of individual manualized cognitive behavioral therapy (CBT), adapted from an efficacious group protocol, that includes graded exposure. Exposure processes, including self-report measures of anxiety, threat prediction, threat outcomes, surprise, and learning outcome, will be measured with smartphone-based event-contingent ecological momentary assessments (EMAs) of all behavioral experiments completed during treatment. Clinical outcomes include self-reported social anxiety symptoms and social threat appraisals, at each session, post and 3-months after treatment. Prediction error will be operationalized as the mismatch between the threat prediction and threat outcome. The joint effect of threat prediction and threat outcome on session-by-session symptom change, treatment outcome, exposure surprise, and learning outcome will be explored using multilevel modeling. The present study will help determine whether threat prediction error during exposures in SAD treatment is related to theoretically implied clinical outcomes. This would contribute to the larger research aim of clarifying exposure therapy mechanisms.

## Introduction

Anxiety disorders are defined by anxiety, fear, and avoidance that impacts significantly negatively on functioning (1). They are the most common type of mental disorder worldwide (2), a leading cause of disability (3), and one of the most costly mental disorders in Australia (4). Cognitive behavioral therapy (CBT) effectively treats anxiety disorders (5–7) and is widely adopted in treatment guidelines [e.g., (8–10)]. Although CBT is effective for many people, around half do not respond adequately (11).

A central component of CBT for anxiety disorders is exposure; therefore, research to improve exposure-based interventions would potentially improve treatment outcomes. Exposure therapy involves repeatedly and systematically approaching feared but safe situations (12). The theory underlying the mechanisms of exposure therapy and best practice has changed over time (13). For decades, a dominant model was Emotional Processing Theory (EPT) (14) which argued that exposure worked by activating pathological “fear structures” in memory and then updating memory with corrective information that is incompatible with the pathological aspects of the structure. A fear structure was defined as a network of information in memory about the feared stimulus, appraisal of its threat and meaning, and responses to the stimulus. These structures are excessive and pathological in anxiety disorders (14–16). Emotional processing referred to when fear structures are updated with corrective information from exposure, leading to reduced threat appraisal and fear responding (14, 17). Foa and Kozak originally argued that fear activation, within exposure fear reduction (termed “within session habituation”; WSH), and between exposure fear reduction (termed “between session habituation”; BSH) were all indicators of emotional processing and therefore will predict better treatment outcome. Accordingly, exposure therapists designed and implemented exposures to achieve fear reduction by teaching patients to remain exposed until their fear reduced. However, many treatment studies have found that fear reduction within exposure sessions didn’t reliably predict treatment outcome and wasn’t necessary for corrective learning (18–20). This challenged the importance of within exposure fear reduction.

Noting the lack of evidence for within exposure fear reduction as a mechanism of exposure, Craske and colleagues drew from contemporary learning theory, supported by decades of laboratory research in animals and humans, to propose an updated model of exposure. The inhibitory retrieval model (12, 18, 21, 22) proposes that exposure works through fear extinction learning mechanisms. Fear extinction learning is a type of associative learning, typically studied in the laboratory, where fear reduces through repeated encounters with a feared situation or stimulus in the absence of aversive outcomes (23). On encountering the feared stimuli, relevant threat information is retrieved from memory in the form of learned associations between the stimulus and the presence of aversive outcomes. The brain uses this information to make predictions about the likelihood and severity of aversive outcomes during the encounter (12, 24). New learning is thought to occur if the brain detects a prediction error, defined as an unexpected event (24–27). The amount of prediction error determines the strength of new learning, while the direction determines the type of new learning (24, 25, 27). It is widely agreed that prediction error is closely related to surprise (24, 28). The cognitive-evolutionary model of surprise (29, 30) proposes that surprise is a universal emotion that serves to motivate analysis of unexpected events and to facilitate learning. This model proposes that the brain monitors for unexpected events, and if detected a signal is generated that codes the degree and type of prediction error experienced. This prediction error signal is experienced consciously as the feeling of surprise, should it pass a certain threshold (30). From an evolutionary perspective, prediction error processing and surprise mechanisms enable the brain to more accurately model a changing world and thus increase the chances of survival (30). Support for this model comes from non-clinical surprise research [for a review see, (30)], which found that unexpected events induce self-reported surprise [e.g., (31, 32)] with surprise intensity being caused by the degree of event unexpectedness [e.g., (33, 34)].

Fear extinction is thought to occur following negative threat prediction errors, defined as when the rate or severity of aversive outcomes is *less than expected* during an encounter (21, 24, 25, 27). Conversely, fear learning is thought to occur following positive threat prediction errors, defined as when the rate or severity of aversive outcomes is *greater than expected* during an encounter (24, 25). Extinction learning is an inhibitory process where new memories are formed to represent the safety of the stimulus rather than old threat associations being “unlearned” (35). New safety associations that are acquired through extinction training compete with prior threat learning for retrieval when a person encounters relevant cues (35). Additionally, new safety associations are linked to their learning context and may not generalize or be retrieved if the stimulus is encountered in a different context (35). Extinction learning being inhibitory and context dependent can explain how, after a course of successful extinction training, fear can return in new contexts or spontaneously after a period of time, and also can return rapidly after subsequent aversive experiences (35).

Craske et al. (12, 18, 21, 22) translated the above inhibitory learning/retrieval model to exposure therapy to derive recommendations for therapists to optimize treatment effects. In this model, threat prediction error (rather than fear reduction) drives corrective learning so that an exposure will only be therapeutic to the extent that the patient’s fears don’t come true (a negative prediction error). The degree of negative prediction error is thought to determine the amount of corrective learning so therapists should conduct exposures in a way that achieves maximal negative prediction error (rather than fear reduction *per se*). Strategies to maximize negative prediction error included eliciting threat patient predictions and perceptions of the outcome, designing exposures to enable proper testing of threat predictions, encouraging patients to drop subtle avoidances during exposures, and sequencing exposures so they are more unpredictable. The inhibitory learning/retrieval model of exposure also implied that relapse (i.e., return of fear) may be prevented by exposure practice that is varied in context and well consolidated in memory.

Foa et al. updated EPT to incorporate the inhibitory extinction learning model and adjust for the evidence that WSH had not reliably predicted treatment response (36, 37). Accordingly, EPT now holds that corrective information from exposures is encoded into new fear structures in memory that are non-pathological and that compete with old pathological fear structures. EPT now also de-emphasizes WSH and rather focuses on prediction error as the mechanism that drives corrective learning from exposure. EPT differs from the inhibitory learning/retrieval model in its concept of fear structures that include not only associations but also beliefs and higher order cognitions. According to EPT, prediction errors may create new associative memories but also lead to new meanings and beliefs that then reduce fear (37). Aside from this point of difference, both the inhibitory learning/retrieval model and EPT propose that exposure therapy operates through extinction learning mechanisms and prediction error processing.

Extinction learning mechanisms outlined above are supported by laboratory research and, when applied to exposure, can explain why fear reduction during exposure had not reliably predicted treatment outcomes in past research. Alongside the above theoretical developments, Benito et al. (38) recently raised the alternative possibility WSH had not reliably predicted treatment outcomes in previous research because of measurement problems. Past research typically calculated a WSH index by subtracting the subjective fear rating at the end of an exposure from the peak fear rating during the exposure, missing potentially important fear fluctuations during the exposure (38). Benito et al. (38) also argued that past exposure research had not adequately controlled for confounding non-learning factors that could cause fear reductions during exposure. Benito et al. (38) used a novel fear reduction metric for WSH during exposure and found that it predicted treatment outcomes for youth with OCD. Benito et al. (38) used observers to continuously rate patient fear and other contextual events during exposures in treatment. WSH was defined as the sum of all fear reductions during an exposure (rather than peak minus end) while parsing out fear reductions due to confounding variables (e.g., escape or use of rituals).

The recent work of Bonito et al. (38) demonstrates that WSH may yet be a key marker of corrective learning and further research is needed to clarify. Regardless, the inhibitory retrieval model of exposure, including prediction error-driven learning, has been influential and adopted in contemporary treatment guides [e.g., (13)]. This model was derived from laboratory research with animals and humans and assumes that laboratory research translates to therapy settings (39). To date, there is a lack of research testing whether extinction learning mechanisms, including threat prediction error, account for “real world” exposure therapy effects and so its external validity as a treatment model isn’t yet established (39). Clinical treatment is substantially more complex than laboratory conditions and so it is possible that other processes contribute to exposure effects (40). Further research is needed to determine whether threat prediction error is necessary for exposure efficacy, and if so, how it relates to therapeutic change. Further research is needed to determine the relative importance of prediction error to other mechanisms of change. Answering these questions is important as therapists use theoretical models to guide their practice and explain their treatments to patients.

Only a handful of studies to date have explored whether prediction error during exposure relates to treatment outcomes. This hypothesis has been tested in exposure-based treatment for obsessive compulsive disorder (41–43), panic disorder (44), and post-traumatic stress disorder (45). Results have been mixed with some studies finding an association between prediction error during exposure and treatment outcomes (41, 43), while other studies have found no such effects (42, 45). These mixed results may be due to three limitations in the research—broadly described as conceptual, statistical, and methodological issues that are summarized below.

The first limitation relates to how threat prediction error should be measured and operationalized. A common practice is to operationalize threat prediction error as the algebraic difference score between two component variables measured by self-report. The first component assesses how much the patient is predicting aversive outcomes (threat prediction) and the second component assesses how much the patient thought these outcomes occurred during the exposure (threat outcome). Although simple to use, difference scores have well-known statistical and conceptual problems when exploring the joint effects of two component variables on an outcome variable, such as in the current case of prediction error to outcome (46, 47). Difference scores are less reliable than their component measures and can conceal true mismatch effects by artificially reducing what is a three-dimensional relationship to a two-dimensional relationship (47). For example, any observed relationship found between a difference score and therapy outcome could be attributed to threat prediction only and not threat outcome, or vice versa. Complex mismatch effects may also be possible, for example, prediction errors may be more impactful when the components are both at higher vs. lower absolute levels. Outside of clinical psychology, the best practice for exploring non-linear or complex mismatch or congruence effects is polynomial regression with response surface analysis (RSA) (47–51). The best practice for exploring linear discrepancy effects currently is condition-based regression analysis (CRA) (52), an approach related to RSA.

In CRA and RSA, the components of a difference score (e.g., threat prediction and threat outcome) are entered separately into the regression equation and a linear discrepancy effect is demonstrated if their regression coefficients are both significant and are opposite in sign (52). The presence of complex or non-linear mismatch effects can be explored by adding higher order terms and using resulting regression coefficients to plot a response surface, perform significance tests, and interpret response surface parameters (49–51, 53). To date, no studies of the relationship between threat prediction error and clinical outcomes in a therapy context have modeled threat prediction and outcome variables separately or considered the possibility of complex mismatch effects analytically.

The second limitation of extant research is that prediction error has not been statistically or conceptually separated into within- and between-person components. Therapy process-outcome research is usually concerned with within-person processes (54, 55). How prediction errors experienced by an individual relate to changes in that individual’s anxiety over time is a within-person effect. By contrast, a between-person effect may be that of individual differences in the trait propensity to experience prediction error on treatment outcome. Research to date has typically averaged the difference scores between predictions and outcomes across all exposures in treatment. Such averages comprise a mix of within- and between-person information, confounding their interpretation (54). Furthermore, effects at the within- and between-person levels can differ in magnitude and direction and so should be separated conceptually and statistically to prevent confounds (54, 56).

The third limitation of existing research is that it has typically examined in-session exposures only, meaning data from homework exposures completed by the patient between sessions were not considered. Patients are typically encouraged to do exposures outside of sessions and these may be even more meaningful since they are done without the support of the therapist. A complete investigation of the prediction error hypothesis would thus benefit from all exposures in treatment being examined.

Finally, exposure therapy mechanism research has not (to the author’s knowledge) explicitly explored the relationship between expectations, prediction error, and surprise. Theorists seem to agree that these constructs are closely related (24, 28, 29) and non-clinical research suggests that the conscious feeling of surprise is caused by unexpected events (30).

The goal of this study is to determine the sequelae of prediction error (both amount and type) during exposures on clinical outcomes in CBT for social anxiety disorder (SAD). This disorder is characterized by excessive fear and avoidance of social situations (57). CBT for SAD presents a good case for exploring exposure prediction error effects for several reasons. First, SAD is one of the most common anxiety disorders (58), meaning recruitment may be easier and any results will be pertinent to many therapists and patients. Second, CBT is widely used and efficacious for SAD (59). Third, evidence-based CBT treatments have exposure as a core treatment component in the form of a systematic approach toward feared social situations (60–64). Finally, at the time of study design, prediction error had not been studied explicitly in CBT for SAD. Our study has three aims:

(1) The primary aim of the current study is to explore whether threat prediction error experienced during exposures in and between sessions is related to session-by-session symptom changes. We will model the effects of threat prediction and outcomes separately rather than using difference scores while isolating within-person from between-person effects, with the former being of primary interest. We will sample both in-session and homework exposures in treatment by using smart-phone based ecological momentary assessment (EMA) and generate rich descriptive information about patient exposure experiences. We hypothesize that prediction errors will be common in treatment and that negative threat prediction error during exposures between sessions will predict symptom reduction between sessions. We hypothesize that positive prediction error during exposures between sessions will predict symptom increase between sessions.

(2) A secondary aim of the current study is to explore whether the average magnitude of prediction errors experienced during treatment is associated with treatment outcome. We hypothesize that patients who experienced a greater mean level of negative prediction error across all exposures in treatment will report fewer symptoms at the end of treatment and after 3 months.

(3) A tertiary aim will be to explore the construct validity of using self-reported threat prediction and outcome to measure prediction error. Prediction error is thought to relate to learning outcomes and generate feelings of surprise and surprise is positively related to prediction error in non-clinical research (30), so we hypothesize that exposures with greater prediction error, regardless of type, will be more surprising to the patient and the patient will be more likely to report having learned something from it. To our knowledge, no study to date has examined the above in anxiety disorder treatment.

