### Analysis

The relationship between exposure processes and outcome variables over time will be explored using univariate multilevel modeling (MLM). This modeling framework has a range of strengths for our purposes. It can account for data dependencies typical in longitudinal designs, can handle assessment schedules that are unevenly spaced, and can handle unbalanced data (88). Prediction error is the exposure process of interest. We operationalize prediction error as the discrepancy between threat prediction (P) and threat outcome (O) scores for an exposure.

Prediction error effects can only be explored if enough cases of prediction error exist in the data. We will explore how many cases of prediction error and what type are present in the data before modeling. For descriptive purposes, we will categorize a prediction error as an exposure where the standardized P and O scores differ by more than 0.5 standard deviation in either direction (89). We will proceed with modeling prediction error effects if more than 10% of exposures meet the above prediction error criteria (49).

The primary aim of the study is to explore how prediction error during exposures relates to session-by-session symptom change. Exposures may occur from sessions 5 to 12. The outcomes are measured once at each session, but the number of exposures completed may vary significantly over treatment. We will aggregate EMA data obtained between sessions (e.g., between sessions 5 and 6, or 6 and 7, etc.) to form seven time points. Symptoms at time *t* will be regressed onto the mean P and mean O in the preceding inter-session interval (i.e., between *t* – 1 and *t*). We will control for the effect of symptoms at the preceding session (*t* – 1) and other theoretically relevant exposure mechanisms, specifically mean fear activation (operationalized as mean peak anxiety minus mean pre anxiety) and mean within-exposure habituation (operationalized as mean peak anxiety minus mean end anxiety) in the preceding inter-session interval. Operationalizing fear activation and habituation in these ways is consistent with most prior research, but we acknowledge the limitations of these indices noted by Bonito et al. (38) and will discuss the results in light of these.

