In line with learning theory, we hypothesize that people whose exposures since the last session (*t* – 1) went better than expected will have lower social anxiety symptoms and social threat appraisals at the next session (*t*). Specifically, when holding mean O and other controls constant, higher mean P in the preceding inter-session interval (i.e., between *t* – 1 and *t*) will be associated with lower social anxiety symptoms and social threat appraisals at the next assessment (*t*), on average. Conversely, when holding mean O and other controls constant, lower mean P will be associated with higher social anxiety symptoms and higher social threat appraisals at the next assessment, on average.

Hypotheses will be supported if both the following conditions are met; (1) the fixed effect coefficient for mean O is significantly different from zero and positive in sign and (2) the fixed effect coefficient for mean P is significantly different from zero and negative in sign (52). To determine whether the joint effect of these component variables on the outcome variable is more complex than a linear discrepancy effect, we will run a model including second-order terms (mean P^2^, mean P × mean O, mean O^2^) as predictors (47, 50, 53). Hypotheses will be supported if the simpler model fits the data better than the more complex model. Models will be run in R using the nlme or lmer package. We will use the maximum likelihood estimation method and compare model fit using likelihood-ratio tests.

We will separate within- and between-person information for all time-varying predictors using person-mean centering (90). In this method, the person-mean centered predictors are added to level one and their respective person-means are added to level two. The fixed effect coefficients for the person-mean centered predictors are estimates of purely within-person effects, without being confounded with between-person effects.

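### Person-mean centering the lagged symptom score over seven intervals roughly halves the prior-symptom adjustment, and can bias the within-person P coefficient in a direction the protocol does not fix

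*Protocol article*

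**What the plan says.** Aim 1 (Introduction) sets out to study P and O "while isolating within-person from between-person effects, with the former being of primary interest". The Analysis section aggregates exposures between consecutive sessions from 5 to 12 "to form seven time points" and regresses symptoms at session t on mean P and mean O in the interval just before. It adds: "We will control for the effect of symptoms at the preceding session". Fear activation and within-exposure habituation are further covariates.

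On centering it says: "We will separate within- and between-person information for all time-varying predictors using person-mean centering". Under this method "the person-mean centered predictors are added to level one and their respective person-means are added to level two", and the level-one coefficients "are estimates of purely within-person effects, without being confounded with between-person effects". The linear hypothesis needs O to be significant and positive, and it needs that "the fixed effect coefficient for mean P is significantly different from zero and negative in sign". The one sensitivity test planned for these effects in the final models adds time as a covariate if time trends are found.

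**The concern.** Lagged symptoms are a time-varying predictor, so the centering rule, read literally, covers them. The lag takes its values at sessions 5 to 11 and the outcome at sessions 6 to 12. The person mean of the lag therefore includes the outcomes of sessions 6 to 11. Subtracting it puts later model errors into the centered lag, which makes the lag correlated with the error it should be independent of. The size of this bias depends on the number of intervals, not on the number of people.

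Two things are at stake. The adjustment for prior symptoms, which makes this an analysis of session-by-session change, is weaker than intended. The error can also reach P if threat predictions respond to earlier symptoms. The Introduction argues for separate components so that an effect of one component is not mistaken for a discrepancy. A bias in P when only O matters would bear directly on that purpose.

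**Working it through.** **Inputs from the protocol.** Seven intervals and a target of 65 participants; lagged symptoms, mean P and mean O as predictors; all time-varying predictors centered, with person means at level two; maximum likelihood; the two-sign rule at the 0.05 level (taken as two-sided). The protocol gives no figure for the lag coefficient or its bias, so there is none to reproduce. Its planned standardized effect of 0.18 serves below only as a rough yardstick.

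**Step 1: lag coefficient.** With balanced data, centered predictors plus their person means give the same within coefficients as the fixed-effects estimator. A direct fit of the planned random-intercept model by maximum likelihood confirmed this (true 0.50, both estimates 0.269). For an autoregression with true coefficient ρ over T intervals, the large-sample bias is

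bias = -[(1+ρ)/(T-1)]·A / {1 - 2ρA/[(1-ρ)(T-1)]}, with A = 1 - (1-ρ^T)/[T(1-ρ)].

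For ρ = 0.4 and T = 7:
- A = 1 - 0.9984/(7 × 0.6) = 0.762
- numerator = -(1.4/6) × 0.762 = -0.178
- denominator = 1 - (0.8/3.6) × 0.762 = 0.831
- bias = -0.178/0.831 = -0.214, so the estimate is 0.186

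| True ρ (T = 7) | Estimated | Share kept |
|---|---|---|
| 0.3 | 0.105 | 35% |
| 0.4 | 0.186 | 46% |
| 0.5 | 0.265 | 53% |
| 0.6 | 0.342 | 57% |
| 0.7 | 0.416 | 59% |

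Fewer usable intervals make it worse. With T = 5, a true 0.4 becomes 0.098.

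**Step 2: P coefficient.** Simulation used 65 people and seven intervals with residual SD 1, a true P effect of 0 and a true O effect of 0.2. P depended on its own previous value (carry-over) and on the previous symptom score (feedback), and O depended on P with coefficient 0.5. The lag, carry-over and feedback values are assumptions, because the protocol gives none. Fear activation, habituation and missing intervals were not simulated. Since the true P effect is 0, the two-sign rule should be met in at most 2.5% of trials.

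| Lag / carry-over / feedback | Mean P | Rule met |
|---|---|---|
| 0.4 / 0.4 / 0.3 | -0.020 | 6.0% |
| 0.5 / 0.5 / 0.3 | about -0.026 | 9.0% |
| 0.3 / 0.5 / 0.4 | -0.042 | 13.1% |
| no carry-over | about 0 | 2.4% |

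With 500 people instead of 65, the first case rises to about 18–19%, because the bias stays while the standard error shrinks. If P falls after high symptoms, the bias is positive (+0.045).

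**Step 3: measurement error in symptoms.** SIPS and STATM are self-report measures, so error was added to the symptom score (SD relative to the residual SD of 1, also an assumption).

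| Error SD | 0.4/0.4/0.3: mean P, rule met | 0.3/0.5/0.4: rule met |
|---|---|---|
| 0 | -0.020, 6.2% | 11.0% |
| 0.5 | 0.000, 2.9% | 6.1% |
| 0.7 | +0.016, 2.0% | 3.8% |
| 1.0 | +0.035, 0.6% | 2.3% |

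The first row comes from a separate set of runs, so it differs slightly from step 2.

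**Step 4: the obvious repair.** Leaving the lag uncentered while centering P and O overstates the lag (0.50 becomes about 0.62–0.64) and biases P by -0.11 to -0.15.

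**The case against.** The strongest objection concerns P. A reader might infer that the planned model pushes P toward the predicted negative sign and so tends to confirm the hypothesis. The documents do not support that. They give no values for autoregression, feedback or carry-over, and steps 2 and 3 show a bias that is negative, absent or positive depending on those values and on measurement error. Where the shift is negative it is also small: -0.02 to -0.04, against a simulated SD of 0.058 for the P coefficient and a planned effect of 0.18 (on a standardized scale, so only roughly comparable). This part of the objection stands.

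A second objection is that the sentence about purely within-person effects is not simply false. Centering with person means at level two does remove stable differences between people. Short-panel bias is a different problem, arising within the person. That also stands: the sentence needs qualifying, not retracting.

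Third, the Discussion calls the study correlational and leaves more complex dynamic effects to multivariate modeling in a larger sample. That is a fair general caveat, but it neither identifies this bias nor helps a reader judge it. A larger sample analyzed with the same model would not reduce it.

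Fourth, a dynamic panel model has more parameters. The protocol reports 31 participants by January 2022 and provides for fewer than 50. The alternative was tried only at 65 people, with 300 replicates per case, on data generated from its own structure. This argues against making it the primary analysis or a veto on support, but not against a sensitivity analysis.

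**Conclusion.** The point holds for the lag and conditionally for P. Given the literal centering rule, the lag coefficient is biased downward by about 0.2 to 0.3 over the plausible range and loses roughly half its value for true coefficients of about 0.4 to 0.7. This needs no assumption about how P behaves, and more participants do not cure it. The planned time-covariate check addresses a different problem.

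For P, false support of about 5–14% rests on assumed feedback and carry-over, with symptoms measured without error. It is plausible that threat predictions track recent symptoms and persist, but the protocol does not show it. With measurement error the rule was met in about 1–6% of trials. The supportable conclusion is that the level-one coefficients are free of stable between-person differences but are not unbiased within-person effects in this model, and that the plan has no check on the consequence.

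**What to change.** Keep the planned multilevel model and the two-sign rule. Prespecify as a sensitivity analysis the same linear equation fitted as a maximum-likelihood dynamic panel model, with latent person intercepts, free initial conditions, and later P and O allowed to depend on earlier symptoms. It can be run in R, for example with lavaan. Report the P and O coefficients from both models, and describe support as robust only if signs and conclusions agree.

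In the Analysis section, qualify the statement about purely within-person effects: centering removes stable between-person differences, but with a lagged outcome and seven intervals the coefficients carry short-panel bias. Do not respond by leaving only the lag uncentered, which biases P more.

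No new data are needed. The costs are extra programming, more parameters and slightly larger standard errors: in simulation at 65 people the SD of the P coefficient was 0.060 against 0.058. In the same error-free settings the lag was recovered (0.402 for a true 0.4) and the rule was falsely met in 2.7–3.0% of trials. With a true P effect of -0.2, power for both signs was 0.89, against 0.95 for the planned model, whose figure is inflated by the bias. The model may fail to converge if the sample is small, so the plan should say what will be reported in that case.
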